	**12. Weight**
	**13. Blood pressure**
	**14. Heart rate**
	15. **History of chronic disease**: History of hypertension, diabetes, cardiovascular disease and other chronic disease; specify current treatment (i.e., medications)
	16. **Chronic pain:** Whether suffer from pain in the past or now, location and degree of pain, the influence of pain in daily life and etc
**BIOLOGICAL SAMPLES** Collected by health workers in community All participants provide samples at local health clinic and some participants go to regional hospital to have MRI scan	17. **Blood samples**: 15 ~ 20 ml venous blood obtained through venipuncture by certified nurses
	18. **Urine samples:** 10 ~ 15 ml fresh urine collected by participants under supervision of researchers
	19. **Faeces samples:** 1 g fresh faeces collected by participants under supervision of researchers
	20. **Hair samples:** 20 hairs over 3 cm obtained by researchers
	21. **Brain MRI scan:** MRI scan of whole brain will be performed after evaluation of psychological health. All high-risk participants are referred for a brain MRI scan at a regional hospital, and low-risk and moderate-risk participants are given the option of a referral for a brain MRI scan
**PSYCHOLOGICAL HEALTH** Self-reported questionnaires, and scales completed by local physicians, and diagnostic assessments by participating psychiatrists All participants come to the local clinic to complete the questionnaires online and are assessed by local clinicians and some participants are administered formal diagnostic examination by a participating psychiatrist	22. **Personality traits:** Big Five Inventory scale
	23. **Coping Style**: Simplified Coping Style Scale
	24. **Loneliness:** UCLA Loneliness Scale
	25. **Depression:** PHQ-9 Depression Scale
	26. **Anxiety:** GAD-7 Anxiety Scale
	27. **Social support:** Multidimensional Scale of Perceived Social Support
	28. **Quality of life:** Quality of Life scale
	29. **Sleep quality:** Insomnia Severity Index
	30. **Evaluation performed by community clinicians and psychiatrists**: Community clinicians will assess the psychological health and risks of depression after participants fill out the self-reported questionnaires. Participants classified as high-risk of depression will be assessed by a psychiatrist (using SCID to determine DSM-5 diagnoses) and undergo a brain MRI scan at a regional hospital (see above)
**OTHER MEASURES** Standard questionnaires and self-report questionnaires, some of which are designed by project researchers Participants come to local health clinic and complete the questionnaires online	31. **Occupation:** Occupation type, working intensity, job satisfaction
	32. **Lifestyle:** Smoking, drinking, exercise, habit, pets and etc
	33. **Childhood exposures:** Raised up by who, family background at childhood, abuse or bullying received as a child or adolescent and etc. Additionally, Child Trauma Questionnaire will be used
	34. **Utilization of mental health services:** Knowledge and demand of mental health services, how many times do participants actually use this resource
	35. **Life events:** Major events in life such as divorce, death of close relatives or friends, and etc. Additionally, Life Events Scale will be used
	36. **Childbearing history (for women):** This variable is designed especially for women, including menstruation, pregnancy, miscarriage, and etc

#### Construction of an online project management system

The online management system for the project includes three components, the Manager, Health Worker, and Participant Modules. The *Management Module* is used by national and regional supervisors to assign participants, allocate research tasks, supervise the research process, and conduct quality-control operations. The *Health Worker Module* is used by local clinicians, psychiatrists, lab technicians, MRI technicians, and researchers who obtain community-level parameters to upload the results of clinical, psychiatric and MRI examinations, to report the collection and analytic results of biological samples (blood, urine, faeces, and hair), and to annually upload the community-level parameters for each of the 34 primary sampling sites. The *Participant Module* is used by participants to register for the study to; complete the self-report questionnaires included in the study; get results of clinical, laboratory and MRI assessments; obtain information about depression and other mental disorders; and get suggestions about how to improve their health.

#### Staff training

The study will be cooperatively managed by 17 mental health institutions and universities around the country, each responsible for research work in one urban community and one rural community. To ensure consistency across the 17 sites, standardized national training of participating researchers and psychiatrists was completed prior to data collection. From July 2022 to August 2022, we organized one online and one in-person training session for researcher staff that included introduction to the aims, procedures, quality control processes, and standardized data collection methods using the online management system. From September 2022 to October 2022, all psychiatrists conducting diagnostic examinations for the study were trained to assess DSM-5 diagnoses using the Structured Clinical Interview for Diagnoses using DSM-5 (SCID-5-CV).

#### Enrollment and baseline evaluation

Residents of the 34 primary sampling sites who meet the inclusion and exclusion criteria will be randomly selected from lists of community members registered in the public health system (described above) and invited to participate in the project. To improve the response rate, prior to the enrolment advertising billboards will be set up at the local health service center and messages introducing the study will be sent to all community members via WeChat (social media) site. Enrollment and baseline data collection included the following steps (see Fig. 2):A)Basic information (e.g., name, age, address, phone number) of residents in the community is extracted from the community health service center (which typically have a registry of virtually all permanent residents in each community).B)Among the permanent residents 18 years of age or older, 3250 individuals will be randomly selected from the registry of residents maintained by the local health authorities.C)Researchers make phone calls to selected residents to introduce the China Depression Cohort Study-I and – if the individual expresses interest in participating – to invite them to the local community health service center for an intake interview. Researchers and community health care workers will make home visits to invite individuals who cannot be contacted by phone.D)When potential participants visit the community clinic they will be provided with details about the project and asked to sign a written informed consent.E)Baseline assessments of consenting participants are typically conducted at the local health clinic on the same day as enrollment. They include the following:Community clinic physicians conduct a physical exam, measuring weight, height, heart rate and blood pressure.Research nurses collect biological samples of blood, urine and faeces.Trained researchers instruct participants in the use of the online Participant Module and supervise their completion of self-report questionnaires about their demographic characteristics, environmental exposures, and mental health symptoms.Community clinic doctors conduct a psychological evaluation using the expanded version of the 12-item General Health Questionnaire (GHQ-12) [34, 35], which consists of the original Chinese version of the GHQ-12, and 12 additional items to improve its sensitivity. The 12 supplemental items include 6 items described in previous studies [34, 36] (respondents' subjective report of their physical health in the past month; respondents' subjective report of their psychological health in the past month; obsessive thoughts or compulsive behaviors in the last month; restriction of activities because of phobias in the past month; feelings of extreme nervousness or anxiety in the last six months; and social problems due to drinking in the last year), and 6 items developed for the current project based on expert consultation (feeling depressed or down for at least two weeks; seeking help from others due to psychological problems; hospitalization due to psychological problems; suicidal behaviors such as self-poisoning or self-injury; intention of self-harm or suicide; family history of mental disorders such as depression). The 12 GHQ-12 items are each scored as 0 (not present or mild) or 1 (present to a moderate or significant degree); so the total GHQ-12 score ranges from 0 to 12. Each participant will be classified as low-risk of depression (a GHQ-12 score of 0 to 1 and none of the 12 additional items present), moderate-risk of depression (a GHQ-12 score of 2 to 4 and none of the 12 additional items present), or high-risk of depression (a GHQ-12 score of at least 5 or a positive score on any of the 12 additional items) [36].Formal diagnostic examination by a psychiatrist using the SCID-5-CV interview schedule will be conducted in all participants classified as high-risk of depression, in 40% participants classified as moderate-risk of depression and in 10% participants classified as low-risk of depression. Similar to other two-stage epidemiological studies [34, 36], higher proportions of individuals at higher risk of depression are administered the definitive diagnostic interview; this method allows for an efficient use of the limited number of psychiatric personnel available while allowing for accurate prevalence estimates for the total population (by estimating the rates of false positive GHQ-12 rates in the high-risk group and rates of false negative GHQ-12 rates in the moderate- and low-risk groups).All high-risk participants are referred for a brain MRI scan at a regional hospital, and low-risk and moderate-risk participants are given the option of a referral for a brain MRI scan.

**Fig. 2 Fig2:**
[figure not shown]
Flowchart of enrollment and baseline assessments

#### Follow-up

The initial duration of follow-up is five years. (The study organizers will subsequently apply for additional funding to transform the study into a continuing cohort project.) The follow-up procedures will be as follows:A)Community-level variables shown in Table 2 (including climatic, environmental and socio-economic characteristics) will be collected annually from national databases for each of the 34 primary sampling sites.B)Participants who do not have any current or past mental disorder (based on the SCID-5-CV interview) at baseline or at subsequent assessments, the following follow-up assessments will be made *annually*.Information about participants’ diagnoses and treatment of diseases in the prior year will be collected in three ways: review of records of the national medical insurance system (which covers all permanent residents); self-reported information about medical treatment for mental disorders; and results of the annual GHQ-12 screening and SCID-CV interviews.Community clinic physicians conduct a physical exam, measuring weight, heart rate and blood pressure.Research nurses collect biological samples of blood, urine and faeces from a sample of 5% of the participants.Repeat MRI scans we be conducted in each participant who had MRI scan at baseline.Online questionnaires will be sent to participants through e-mail or WeChat. Participants unable to use this online system will be invited to visit the local health clinic where they will be given equipment and any assistance needed to complete the questionnaires.Trained researchers will make phone calls to those who don’t respond to the online questionnaires and to those who self-report as being at high risk of a depressive disorder at any time over the prior year. Participants classified by the researcher as ‘high-risk of depression’ at any time in the prior year will be encouraged to attend an appointment with a psychiatrist at the community clinic or local general hospital.Psychiatrists will perform SCID-5-CV diagnostic assessments of the invited participants who agree to the interview.C)For participants diagnosed with current or past depressive disorder or other psychiatric disorder based on SCID-5-CV interviews by a psychiatrist at baseline or during follow-up assessments the following follow-up assessments will be conducted.Every 3 months, telephone calls will be performed by trained researchers to check their depressive symptoms, thoughts of suicide or self-harm, suicide attempts or other self-harm behaviors, social functioning, and mental health treatments over the prior 3 months. Individuals classified by the researcher as ‘high-risk of depression’ who have never been diagnosed with a depressive disorder (only had other diagnoses) or have fully recover from a prior episode of depression (i.e., at least 2 months of no clinically significant symptoms) will be encouraged to attend an appointment with a psychiatrist at the community clinic or local general hospital.A psychiatrist will conduct a repeat diagnostic exam (using the SCID-5-CV interview) with invited participants who agree to the interview to determine whether a new-onset major depressive disorder has occurred in the prior 3 months.Each year information about participants’ diagnoses and treatment of diseases (including treatment for mental disorders) from hospital records will be collected from regional hospitals and from the national public health system.Each year community clinic physicians conduct a physical exam, measuring weight, height, heart rate and blood pressure.Each year the standard online questionnaire will be sent to these participants through e-mail or WeChat. Participants unable to use this online system will be invited to visit the local health clinic where they will be given equipment and any assistance needed to complete the questionnaires.Each year research nurses collect biological samples of blood, urine and faeces from participants with a current or lifetime depressive disorder (but NOT from individuals who only have other, non-depressive, mental disorders).Each year, participants with a current or lifetime depressive disorder (but NOT from individuals who only have other, non-depressive, mental disorders), are referred for a brain MRI scan at a regional hospital.

**Table 2 Tab2:** Environmental level variables at each of the 34 study communities

TYPE OF DATA Source of data Collection method	Variables
**CLIMATE** Official website of China Meteorological Administration Researchers record data for the 34 sites each season each year	1. **Temperature:** Lowest, highest, and average temperature per season
	2. **Precipitation:** Lowest, highest, and average precipitation per season
	3. **Sunshine:** Lowest, highest, and average time of sunshine per season
	4. **Climate alert:** Types and frequencies of climate alerts per season
	5. **Natural disasters**: Intensity and duration of natural disasters, including floods, forest fires, earthquakes, mud-rock flow, and typhoons
**NATURAL ENVIRONMENT** Official website and annual report of Ministry of Ecology and Environment Researchers record data for the 34 sites each season each year	6. **Noise:** Days noise level exceeds standard level, average intensity of noise, type of noise
	7. **Atmospheric environment:** Lowest, highest and average level of air pollution index (e.g., PM 2.5, SO_2_), average days air quality rated as ‘good’ or better
	8. **Water environment:** Water quality and nutrition index of main rivers and lakes
	9. **Soil environment:** Amount and quality of cultivated area
	10. **Radiation:** Intensity of ionizing radiation and electromagnetic radiation
	11. **Pollution:** Amount and type of waste discharged into the environment, including but not limited to solid waste, car exhaust, industrial waste
**SOCIOECONOMIC CHARACTERISTICS** Official website of National Bureau of Statistics and China Statistical Yearbook Researchers calculate socioeconomic indexes based on data provided in the two sources	12. **GDP index:** Total and per capita GDP
	13. **Aging index:** Proportion of population aged over 60 years old
	14. **Poverty gap** Proportion of population living below local poverty level

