**Methods:**

A multistage stratified random sampling method will be used to identify a nationally representative community-based cohort of at least 85,000 adults (i.e., ≥ 18 years of age) from 34 communities in 17 of mainland China’s 31 provincial-level administrative regions. Baseline data collection includes 1) demographic, social and clinical data, 2) diagnostic information, 3) biological samples (i.e., blood, urine, hair), 4) brain MRI scans, and 5) environmental data (e.g., community-level metrics of climate change, air pollution, and socio-economic characteristics). Baseline findings will identify participants with or without depressive disorders. Annual reassessments will monitor potential risk factors for depression and identify incident cases of depression. Cox Proportional-Hazards Regression, Network analysis, Disease trajectory modelling, and Machine learning prediction models will be used to analyze the collected data. The study’s main outcomes are the occurrence of depressive disorders; secondary outcomes include adverse behaviors (e.g., self-harm, suicide), the recurrence of depression and the incidence other mental disorders.

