Cohort studies about depression in China include small-sample studies focused on perinatal depression [26, 27] and large-sample studies that piggy-back on cohorts collected for other reasons such as The China Hainan Centenarian Cohort Study (CHCCS) and the China Kadoorie Biobank (CKB) study [28, 29]. These prior studies in China concentrated on the consequences of depression, not on the causes of depression. There is no nationally representative longitudinal cohort study of depression in China.

Most of the currently available cohort studies about depression have serious limitations. 1) The studies often include patients with depression at baseline, so they tend to focus on the outcomes of treatment rather than on the causes of the disorder. 2) Very few studies consider community-level environmental factors such as local impacts of climate change, level of urbanization, socio-economic status of the community, availability and quality of health services, and patterns of health-seeking behavior for mental disorders. 3) None of the available studies consider the role of dynamic interactions between community-level environmental factors and the characteristics of individual community members (such as genetic susceptibility, neural circuits and intestinal flora) on the onset and course of depressive disorders. And 4) few cohort studies propose or test predictive models about the mechanisms that result in depressive disorders.

The China Depression Cohort Study will address most of these limitations. It will recruit a representative community-based cohort of at least 85,000 adult individuals (the China Depression Cohort Study-I) and a school-based cohort of at least 15,000 middle school students 12 years of age or older (the China Depression Cohort Study-II). This report is a detailed protocol of The China Depression Cohort Study-I (hereafter referred to as “this study”).

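### Both follow-up branches are defined by SCID-5-CV result, but many participants get no baseline SCID, so cases present before enrolment can be counted as incident depression

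*Protocol article*

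**What the plan says.** Under Enrollment and baseline evaluation, the expanded GHQ-12 sorts participants into low, moderate and high risk of depression. High risk means "a GHQ-12 score of at least 5 or a positive score on any of the 12 additional items". The SCID-5-CV "will be conducted in all participants classified as high-risk of depression", and "in 40% participants classified as moderate-risk of depression and in 10% participants classified as low-risk of depression". The stated reason is efficient prevalence estimation, which includes estimating "rates of false negative GHQ-12 rates in the moderate- and low-risk groups".

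The Follow-up section then splits the cohort by SCID result. Item B (annual assessment) covers "Participants who do not have any current or past mental disorder (based on the SCID-5-CV interview) at baseline or at subsequent assessments". Item C (calls every 3 months plus yearly assessments) is "For participants diagnosed with current or past depressive disorder or other psychiatric disorder based on SCID-5-CV interviews".

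The abstract's Methods paragraph says: "Baseline findings will identify participants with or without depressive disorders". Outcome measurements makes depression the primary outcome and lists relapse after recovery as a secondary one. Data analyses plans incidence estimates and Cox regression for the diagnosis of depression.

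**The concern.** The branch rule needs a SCID result that the baseline design does not collect for 60% of moderate-risk and 90% of low-risk participants. The text does not say which branch they join.

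The natural default is the annual branch. People there are then treated as free of current and past disorder without having been interviewed, although the design itself expects some cases among them. If such a person screens high-risk later and has a positive SCID, nothing in the article separates a new episode from one already present at enrolment, or a first episode from a recurrence.

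Three things are at stake:
- Early incidence would be biased upward.
- Questionnaires and biosamples taken during an unrecognised episode would be analysed as antecedents of onset.
- An unrecognised past case who recurs would count towards the primary outcome, although the protocol treats relapse as secondary.

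The branch also decides how often a person is contacted and whether yearly biosamples and MRI are sought, so the assignment affects the data collected as well as their analysis.

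**Working it through.** **The plan's own figure.** The Sample size section gives 79,986 for a prevalence of 2.1% with a 95% interval of 2.0% to 2.2%. An exact (Clopper-Pearson) interval of total width 0.002 needs 79,985.3, rounded up to 79,986, so the figure reproduces. It concerns precision of prevalence and says nothing about who is at risk of onset.

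**Inputs from the protocol.** Cohort 85,000; prevalence 2.1%; SCID fractions 100%, 40% and 10%.

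**Assumptions, not in the protocol.** Stratum shares H (high), M (moderate) and L (low); the share s of current cases that screen high-risk; the share f of the remaining cases that fall in the moderate stratum; annual incidence; the fraction of hidden cases found in year 1. The period behind the 2.1% is not stated, and it is treated here as current prevalence.

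**Step 1: participants without a baseline SCID.** Share = 0.9L + 0.6M.
- H/M/L = 10/10/80: 0.72 + 0.06 = 0.78, or 66,300 people.
- 20/20/60: 0.54 + 0.12 = 0.66, or 56,100.
- 30/20/50: 0.45 + 0.12 = 0.57, or 48,450.
- 40/20/40: 0.36 + 0.12 = 0.48, or 40,800.

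At least half lack a SCID as long as 0.9H + 0.3M ≤ 0.4. At M = 10% that means H up to about 41%; at M = 20%, about 38%.

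**Step 2: hidden current cases.** Expected current cases = 85,000 × 0.021 = 1,785. Hidden = 1,785 × (1 − s) × [0.6f + 0.9(1 − f)].
- s = 95%, f = 70%: 89.25 × 0.69 = 62.
- s = 90%, f = 50%: 178.5 × 0.75 = 134.
- s = 80%, f = 50%: 357 × 0.75 = 268.
- s = 70%, f = 30%: 535.5 × 0.81 = 434.

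Undetected past disorder, which item B also excludes, would add to these counts.

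**Step 3: share of year-1 events.** At 1% incidence there are about 850 true onsets. If half the hidden cases are found in year 1:
- Low end: 31 / (850 + 31) = 3.5%.
- High end: 217 / (850 + 217) = 20%.

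The share depends strongly on the assumed incidence. At 0.3% (255 onsets) the same counts give 31/286 = 11% and 217/472 = 46%.

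**Step 4: can the baseline weights repair this?** Weights of 1, 2.5 and 10 (the inverses of 100%, 40% and 10%) recover population prevalence from the interviewed subsample. They do not say which uninterviewed individuals are cases, and a Cox risk set needs that for each person.

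**The case against.** Read together, the two items can only mean that anyone without a SCID diagnosis is followed annually, and the annual procedures suit such people. That stands: a reader might infer that uninterviewed participants have no follow-up at all, and the text does not support this. What is defective is the stated criterion.

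The screen is also a real safeguard. One positive answer on any of 12 added items leads to SCID. These items include two weeks of depressed mood, help-seeking, hospitalisation and suicidal behaviour, so a hidden case must deny them all and score 4 or less on the GHQ-12. Table 1 also collects PHQ-9 and use of mental-health services from everyone. This limits contamination, possibly to the low end of the range, but it does not remove it, since the protocol itself plans to estimate false negatives.

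It can further be said that defining a risk set belongs in an analysis plan. That is fair for the model. The branch rule is a field procedure, however, and an analysis plan cannot recover an onset date that was not asked for at interview.

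Two stronger readings should be resisted. That most participants lack a SCID is not stated; it fails if the high-risk group is above roughly 34% to 44% (M from 30% down to 0%), which the broad any-item rule makes possible. Nor does the Background remark on earlier cohorts, "The studies often include patients with depression at baseline", show the plan contradicting itself: the complaint there is that such studies drift towards treatment outcomes, not that a two-stage screen leaves some cases misclassified.

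**Conclusion.** The point holds. The branch rule cannot be applied as written to participants without a baseline SCID, and the abstract claims a separation at baseline that the design does not achieve for them. Under the default reading, nothing in the article keeps an episode or past disorder present at enrolment out of the incident events.

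The uninterviewed share is about 48% to 78% for an assumed 10% to 40% high-risk. The bias itself cannot be sized from the document. The 60 to 430 hidden current cases assume that 70% to 95% of 1,785 cases screen high-risk. The 3% to 20% of year-1 events further assumes 1% incidence and half of hidden cases found in that year. These figures are illustrative, and no single contamination figure should be quoted as established.

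**What to change.** 1. Reconcile the Enrollment and Follow-up sections: state that item B covers everyone without a SCID diagnosis, including those not selected for SCID. Correct the abstract sentence to match.
2. At every follow-up SCID, record the onset date of the episode and any prior episode. Exclude from incident events, and from the risk set, anyone whose first episode began before their own enrolment.
3. Report sensitivity analyses:
   - (a) baseline SCID-negative participants only, weighted 1/2.5/10;
   - (b) without events in the first year after each person's own enrolment, since drop-outs are replaced annually and entry dates differ;
   - (c) without uninterviewed participants who have a high baseline PHQ-9 or reported mental-health treatment.

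Cost: protocol wording, added fields in interviews already planned, and three analyses. No extra interviews are required. Some events are lost, onset dates rely on recall, and the weighted analysis is less precise. Prevalent cases that are never detected stay in the main risk set, which is why the sensitivity analyses are needed. The fields should be in place before follow-up interviews begin, because onset dates are hard to recover later.

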#### Data analyses

Three main analyses will be conducted. P values of < 0.05 will be considered statistically significant.

The first set of analyses will describe the characteristics of participants and the detailed epidemiology of depression, including the prevalence, incidence, regional characteristics, and trends in the demographic characteristics of depression over time. Means and standard deviations will be used to describe continuous variables, and numbers and percentages will be used to describe categorical variables. Poststratification weights will be used to estimate the national prevalence and incidence of depression. Latent variable analyses and disease trajectory analyses will be used to describe the changes of depressive disorders over time.

The second set of analyses will 1) identify risk factors that influence the onset, severity and course of depressive disorders; 2) identify characteristics that can help distinguish distinct subtypes of depression; and 3) assess potential pathophysiological mechanisms that link the different types of factors associated with depression – external environmental factors, social factors, psychological factors, and biological factors. T-tests, analyses of variance, Kruskal–Wallis tests and Chi-square tests will be used to analyze differences between groups. Correlation analyses will be used to check correlations between variables. To identify potential risk factors for depression, Cox regression analyses will be used to estimate the hazard ratios (HRs) of the association of specific bio-psycho-social risk factors with the diagnosis of depression. Logistic and liner regression will be used to identify factors associated with the severity or depressive episodes. Genomic analysis (including GWAS analysis, Mendelian Randomization), metabolomic analysis and gut microbiome analysis may also be used to explore potential biological mechanisms of depression.

The third set of analyses will use the findings about risk factors to generate and test different prediction tools of depression. Different predictive models will be generated using machine learning algorithms, including Support Vector Machine, Decision Tree and Random Forest algorithms [37, 38]. Performance of the different models will be compared using the area under the receiver operating curve, prospective prediction results (sensitivity, specificity, accuracy, positive predictive value, negative predictive value) and decision curve analysis (DCA) [38].

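### First depression is sought every 3 months in people with another mental disorder but yearly in people with none; if both routes feed the Cox outcome, the hazard ratio for having another disorder will tend to be inflated by an unknown amount

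*Protocol article*

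**What the plan says.** The protocol article, Follow-up, sets two schedules according to SCID-diagnosed mental-disorder status.

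- **Item B, no current or past mental disorder.** Assessment is annual. An online questionnaire comes first. A researcher telephones only people who do not respond or who report high risk at some time in the past year. Those the researcher rates high-risk are encouraged to see a psychiatrist. Diagnoses also come from national insurance records, self-report and an annual GHQ-12 screen.
- **Item C.** This applies "For participants diagnosed with current or past depressive disorder or other psychiatric disorder based on SCID-5-CV interviews by a psychiatrist", at baseline or later. "Every 3 months, telephone calls will be performed by trained researchers to check their depressive symptoms". The people referred from these calls include those "who have never been diagnosed with a depressive disorder (only had other diagnoses) or have fully recover from a prior episode of depression". The repeat SCID is done "to determine whether a new-onset major depressive disorder has occurred in the prior 3 months". Annual records come from regional hospitals and the public health system. The standard online questionnaire is sent each year, but item C does not name the GHQ-12.

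Other sections describe one annual route. The Abstract (Methods) says "Annual reassessments will monitor potential risk factors for depression and identify incident cases of depression". Outcome measurements describes screening and referral at each annual assessment and does not mention the 3-monthly calls. Data analyses says "Cox regression analyses will be used to estimate the hazard ratios (HRs) of the association of specific bio-psycho-social risk factors" with the diagnosis of depression, and does not say which route the diagnosis may come from.

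**The concern.** Among people who have never had depression, how often and by what means a first episode is looked for depends on whether they have another mental disorder, which itself predicts depression. An episode that begins and ends between annual contacts can be missed in item B, whereas item C offers four chances a year to catch it. More complete detection in one group looks like higher incidence in that group. Aim 1 is to identify risk factors for onset, so a hazard ratio for comorbid disorder that partly reflects surveillance would bear directly on a main result. This is a data-collection choice: if the two groups share no assessment, later analysis cannot create one.

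**Working it through.** The article states no incidence, hazard ratio or detection rate, so there is no figure of its own to reproduce on this point. Its one computed figure, the sample of 79,986 for a prevalence of 2.1% with a 95% interval of 2.0% to 2.2%, reproduces with the exact Clopper-Pearson interval but does not bear on this question.

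**Inputs from Follow-up:** contact interval T = 12 months (item B) and T = 3 months (item C); 5 years of follow-up.

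**Assumptions, none given in the documents:** episode duration exponential with mean m months; onset uniform within the interval; an episode that ended before contact is still reported with probability r; true hazard ratio 1.

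**Formula.** The chance that an episode is still present at contact is a(T) = (m/T)(1 − exp(−T/m)). The detection probability is D(T) = a + (1 − a)r. The apparent hazard ratio is about D(3)/D(12).

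**Worked case, m = 6.**
- a(3) = 2 × (1 − exp(−0.5)) = 0.787.
- a(12) = 0.5 × (1 − exp(−2)) = 0.432.
- With r = 0: 0.787/0.432 = 1.82.
- With r = 0.5: D(3) = 0.787 + 0.213 × 0.5 = 0.893, D(12) = 0.432 + 0.568 × 0.5 = 0.716, and the ratio is 1.25.

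Apparent hazard ratio when the truth is 1:

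| Recall of ended episodes | m = 3 | m = 6 | m = 12 |
|---|---|---|---|
| 0% | 2.58 | 1.82 | 1.40 |
| 50% | 1.31 | 1.25 | 1.15 |
| 90% | 1.04 | 1.04 | 1.03 |
| 100% | 1.00 | 1.00 | 1.00 |

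**Check by simulation.** Cox models were fitted to detection dates over 60 months (8 runs of 60,000 people, assumed incidence 2% a year, 15% with another disorder). For m = 3, 6 and 12 they gave 2.68, 1.88 and 1.42 with no recall; 1.32, 1.25 and 1.17 at 50%; 1.11, 1.09 and 1.04 at 80%; and 1.00 to 1.02 with perfect recall. A true hazard ratio of 2 became 2.3 to 2.7 at 50% recall.

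**Timing alone.** The perfect-recall runs isolate the effect of dating onset at detection: at most about 1.02. Missed episodes drive the bias.

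**Correlated factors.** Suppose 20% of people exposed to some factor, and 10% of those unexposed, have another disorder. With a surveillance ratio of 1.25, the factor's spurious hazard ratio is (1 + 0.20 × 0.25)/(1 + 0.10 × 0.25) = 1.05/1.025 = 1.02. With a ratio of 2.58 it is (1 + 0.20 × 1.58)/(1 + 0.10 × 1.58) = 1.316/1.158 = 1.14.

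**Equal schedules.** If T and the method are the same for everyone, D cancels and the ratio is 1.00 for any m and r.

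**The case against.** The strongest reply is that item B is not a snapshot. It asks about the whole prior year and adds an annual insurance-record review covering all permanent residents. That stands, and it removes the most alarming reading. A reader might infer a threefold inflation by assuming that annual contact sees only current or past-month symptoms: for a 3-month episode, (3 + 1)/12 = 0.33 caught yearly against all caught quarterly. The one-year look-back contradicts that assumption. It does not remove the bias, because recall of ended episodes is unlikely to be complete and insurance records find treated cases only.

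Second, a common annual screen may already be intended. Item C participants receive the standard online questionnaire each year, and Outcome measurements does not exempt them from annual screening. A reader might infer that item C has no annual GHQ-12; the documents do not establish that. They leave it unclear: the screen is named only in item B, and at baseline community doctors administer it separately from the self-report questionnaires.

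Third, Data analyses does not name comorbid disorder as an exposure or say that 3-monthly detections count as events, and a condensed article may leave risk sets and event coding to a fuller document. This is why the conclusion is conditional. The unequal collection and the differing descriptions of ascertainment are nevertheless in the article itself.

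**Conclusion.** The concern holds in conditional form. Follow-up ties the search for a first depression to mental-disorder status, and other sections describe a single annual route. If 3-monthly detections enter the Cox outcome, the bias in the hazard ratio for another mental disorder runs upward unless annual recall is perfect. Its size cannot be derived from the documents: about 1.4 to 2.6 with no recall, 1.15 to 1.3 at 50% and close to 1.0 at 90% or more, all resting on assumed episode lengths and recall.

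Two further inferences are not supported. Coarser event dates in item B are not a material second source of bias. Nor would trauma, insomnia or family history be distorted to a similar degree; under the illustrative shares above their shift is small at moderate recall. The point should be settled before follow-up starts but does not undermine the cohort as a whole.

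**What to change.** 1. Reconcile Follow-up with Outcome measurements and the Abstract, and state whether diagnoses reached through the 3-monthly calls count as incident depression.
2. State that item C participants receive the same annual GHQ-12 screen and the same insurance-record review as item B.
3. Base the primary onset hazard ratios on that common annual assessment for everyone.
4. Leave the 3-monthly calls unchanged, and use their detections for course, relapse and secondary analyses.
5. Add a sensitivity analysis that excludes people with a non-depressive disorder at baseline, or stratifies by baseline schedule. Stratifying by a time-updated schedule is a poor choice for the main analysis, because developing another disorder may lie on the path from a risk factor to depression.

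The cost is a few sentences, one screen and one record source to be confirmed or added in item C, and one extra analysis. Some onsets found only by the 3-monthly calls would not count in the primary hazard ratios. Some difference may also remain, because people telephoned quarterly and told their diagnosis may recall and report later episodes better. The article reports only pilot work under way, so the change is cheapest now.
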